**Figure 1. SSI rates as measured by data collectors and auditors, by hospital**

Among 5,093 live births that occurred pre-intervention (control condition) and pre-audit launch, defined as September 1, 2022.

[figure not shown]

Given the literature, we expect that Ethiopian hospitals in the control condition will show some variation in SSI rates, forming a roughly normal distribution about a mean of 9% to 12%. The data from the auditors (right hand axis in figure 1) appears much more likely to have been drawn from this distribution. The one hospital below 3% is concerning for undercounting infections, but not impossible.

The data collected by auditors is subject to recall bias, as they were collected up to a year after the birth. A study on recall bias in Ethiopian women undergoing caesarean section showed that women are less likely to report complications the further they recede in time. In our circumstances, this means that the auditor's data likely underestimates the SSI, since they required longer recall. Since the auditors began in September 2022, most of the cases with long-term recall were in the control condition, which would lower the baseline estimate of SSI. This biases the data against rejecting the null hypothesis, which is a conservative bias.

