| Did your wound open up?                | Yes / No                                            | 
Did the surgical wound open spontaneously (dehiscence)?
NOTE: This does NOT include normal postoperative suture removal at a clinic visit, only if a wound opened up due to infection.
 
Mark 'yes' if the patient reports the skin of a wound or incision opening spontaneously or the skin of a wound being opened by a provider due to an infection.
 
Mark 'no' if the skin of the surgical wound remains closed.
                                                              |
| Is there drainage from the wound?      | Yes / No                                            | 
Did any fluid drain from the wound?
 
Mark 'yes' if the patient reports any liquid or fluid draining from the wound now or since discharge from the hospital.
 
Mark 'no' if no drainage ever occurred from the wound following discharge from the hospital.
                                                                                                                                                                                                                           |
| If yes, What kind of drainage?         | Serous
Pus
Bloody
Feculent
Other: _____ | 
Serous = clear, pinkish or yellowish fluid
           Pus = white, cloudy, green or thick fluid
           Bloody = red liquid blood or clots
           Feculent = brown, liquid or solid feces
           Other = please describe if none of the above fit the description
 
***You may need to ask the patient or family multiple questions to determine the type of drainage from the wound. Please ask follow up questions until you are sure of the type of drainage.
 |
| Have you visited a healthcare provider | Yes / No                                            | Did the patient visit any healthcare provider since discharge from the hospital?                                                                                                                                                                                                                                                                                                                                                                                                                        |

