| 4      | 2,002                  | 1,981                 | 99%            | 783                   | 39%            | 1,087                  | 947                   | 87%            | 607                   | 56%            |
| 5      | 1,576                  | 1,542                 | 98%            | 848                   | 53%            | 413                    | 361                   | 87%            | 222                   | 54%            |
| Total  | 5,715                  | 5,561                 | 97%            | 2,764                 | 48%            | 4,951                  | 4,592                 | 93%            | 2,828                 | 57%            |

30-day follow-up was lower among the auditors compared to the data collectors, with only 48% of patients followed up in the control condition and 57% in the intervention condition. Because the phone calls happened toward the end of the study, the calls in the intervention condition were much closer temporally the enrolled patients' operations compared to the calls to patients enrolled in the control condition, which made it difficult for the auditors to reach control-period patients.

While we recognize measurement problems with both the data collectors' and auditors' data, after consideration we decided to use the auditors' data for all follow-up measures, which include the primary outcome. We will construct some sensitivity analyses to test this decision, as described below. As we have also lost power within the study due to this loss to follow-up, we will add a sensitivity analysis using multiple imputation for the dependent variable to help recapture some statistical power, as described below.

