## 7. General statistical considerations

### 7.1. Modeling

As stated in our protocol, we will use the statistical approach recommended by Hemming and colleagues. To estimate how the intervention is correlated with outcomes, we will fit a mixed effects logistic regression model of the form:

$$Outcome_{ij} = \beta_0 + \beta_1 Month + \beta_2 Intervention + \beta_x X + \mu_i + \varepsilon_{ij}$$

Where:

|                       |                                                                                                                                                     |
|-----------------------|-----------------------------------------------------------------------------------------------------------------------------------------------------|
| Outcome ij | Binary variable for the j th patient in the i th cohort, where 1 = had the adverse outcome, and 0 = did not have the outcome. |
| Month                 | Fixed categorical variable with 18 levels, one for each month. Reference category will be either the first or last month of the study.              |
| Intervention          | Fixed binary variable, where 1 = procedure occurred under intervention condition, 0 = procedure occurred under control condition.                   |
| X                     | Vector of fixed demographic and clinical controls                                                                                                   |
| β 0-x      | Set of regression coefficients                                                                                                                      |
| μ i        | Random effect for cohort                                                                                                                            |
| ε ij       | Error term for the j th patient in the i th cohort                                                                            |

Since this is a cross sectional design (no repeated measures on patients over time), we will not need to account for patient-level correlation over time. The random effect for cohort will account for the within-cluster variance, assuming one shared ICC. We will consider adding a random cohort-by-month interaction term, which would allow for different within-period and between-period ICCs.

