### 9.5 Sensitivity to recall bias

For the audited results, we expect that patients in the control condition had to recall further back in time compared to the intervention patients. This may bias our results if longer recall periods lead to underreporting of forgotten SSI events.

First, using the CS population with follow-up, we will calculate the number of days between the operation and an auditor's follow-up call that succeeded in capturing the SSI data. We will report means, medians, and IQRs across the arms, as well as construct histograms of this follow-up time. This will show by how many days the recall period differed across arms.

Next, we will calculate the SSI rate by month of this recall time, in the control condition only. We expect to see the SSI rate decline at the longer recall periods, allowing us to assess the degree of suppression introduced. We focus here on the control condition because the results from the intervention condition may be confounded by lower SSI rates due to the impact of the intervention rather than faulty recall.

These steps will allow us to assess the bias likely introduced by any differences in recall. We expect that any bias will be conservative against our intervention, since it will likely suppress SSI rates in the control condition more than the intervention, making it more difficult for the study to detect an effect of the intervention. This may help us interpret the results of aim 1.

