## **10 Limitations**

Because we are opting to use data collected by auditors retrospectively up to one year after the enrolled patient’s initial operation, a key limitation in our study is recall bias. In a prior study assessing the roll of recall bias in evaluating complications after surgery in Ethiopian woman undergoing caesarean section, women were less likely to recall complications 6 months after their operation. As a result, our study cohort is more likely to remember complications at the end of the study, after the intervention, than at the beginning of the study before the intervention, in the control period. We believe this limitation is likely to bias us against finding a reduction in SSI associated with our outcome.

Additionally, loss to follow-up is a major limitation. Nearly half of patients could not be reached for their 30-day follow-up phone call by the auditors. However, in comparing demographic and clinical characteristics of these patients, they were not substantively different from our complete dataset. Sensitivity analyses to address loss to follow-up are described in Section 9.4.

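### The SAP calls recall bias conservative, but that direction is not established for the month-adjusted primary odds ratio, and the planned recall check cannot establish it

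*Combined protocol and SAP*

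**What the plan says.** After doubts about the original phone follow-up, general practitioners (the auditors) called all patients again between September 2022 and March 2023 (SAP 4.1). SAP 4.3 reports that "we decided to use the auditors' data for all follow-up measures, which include the primary outcome".

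SAP 4.2 notes that most long-recall cases were in the control condition and concludes: "This biases the data against rejecting the null hypothesis, which is a conservative bias". SAP 9.5 is softer: "We expect that any bias will be conservative against our intervention". So is SAP 10: "We believe this limitation is likely to bias us against finding a reduction in SSI". On the length of recall, SAP 4.2 says of the auditor data that "they were collected up to a year after the birth"; sections 4.3 and 10 give the same limit.

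The primary model (SAP 7.1) has a random effect for cohort and a month term defined as "Fixed categorical variable with 18 levels, one for each month". The Aim 1 outcome is SSI within 30 days (SAP 8.2). The recall check in 9.5 describes surgery-to-call time by arm, and then "we will calculate the SSI rate by month of this recall time, in the control condition only".

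The data dictionary's phone guide says to mark drainage as present "if the patient reports any liquid or fluid draining from the wound now or since discharge from the hospital". The outpatient form records the dates of surgery, discharge and call, but no date of onset.

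**The concern.** The conservative label rests on a difference in recall between whole arms. A stepped-wedge model with month effects does not use that comparison; it mostly compares cohorts that are in different conditions in the same surgery month. A bias that is large and conservative in the crude data may be nearly absent from the adjusted OR, or may have either sign.

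Section 9.5 says its checks may inform the reading of Aim 1. If the label is accepted, a positive result looks safer than it is, and a null result can be put down to forgetting. The planned table would seem to support the label without being able to test it.

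**Working it through.** **Inputs.**
- Enrolment August 2021 to January 2023 (SAP 3.2); audit calls September 2022 to March 2023 (SAP 4.1).
- Implementation dates 28 Dec 2021, 1 Mar, 9 May, 11 Jul and 13 Sep 2022 (Table 2); a run-in of 4 to 6 weeks (SAP 3.2), taken as 5.
- Auditor counts by cohort (Table 4): control 111, 422, 600, 783, 848; intervention 545, 851, 603, 607, 222. These sum to 2,764 + 2,828 = 5,592, while the Table 3 row totals sum to 5,525; I used the arm counts.
- Rates of 12% and 9% from the protocol's power section. True OR = (0.09/0.91)/(0.12/0.88) = 0.725.

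**Assumptions, because the documents give no figure.** Even accrual; 80% of SSIs arise after discharge (SAP 4.1 says only that most do); 6% of these forgotten per month; late events of 0.5 points per month where the open window is examined; three call orders. Cohort is fitted as fixed effects in place of the random intercept.

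**1. The plan's figures and premise.** Follow-up is 2,764/5,715 = 48.4% and 2,828/4,951 = 57.1%, as in Table 4. The crude premise also holds. Of audited women already more than 6 months past surgery on 1 September 2022, about 1,922 are control and 45 intervention, so 1,922/1,967 = 98% are control. Mean recall is about 11 months in control and 3 to 4 in intervention.

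**2. The interval.** From August 2021, September 2022 is 13 calendar months later and March 2023 is 19. A limit of one year does not fit these dates.

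**3. What the model compares.** Both conditions occur together only in surgery months February to September 2022. Within those months the mean recall gap is at most 0.3 months if call timing does not depend on cohort. If early cohorts were called first, control recall is longer by about 3 to 4 months. If late cohorts were called first, intervention recall is longer by about 2 to 4 months.

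**4. Effect on the OR**, with 6% recall loss per month:

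| Call order | Model | True OR 0.725 | True OR 1 |
|---|---|---|---|
| Same in all cohorts | Crude | 1.07 | – |
| Same in all cohorts | Cohort only | 1.12 | – |
| Same in all cohorts | Cohort + month | 0.734 | 1.005 |
| Early cohorts first | Cohort + month | 0.771 | 1.059 |
| Late cohorts first | Cohort + month | 0.699 | 0.953 |

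The crude OR is inflated by 1.07/0.725 = 1.48. In the planned model the factor is 0.771/0.725 = 1.06 or 0.699/0.725 = 0.96, depending on call order. The same-timing row largely restates its own assumption: it shows the mechanism and measures nothing in this trial.

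**5. Open event window.** With late events alone, a true null and the same call timing, the crude OR is 0.73, which is anti-conservative, and the planned model gives 0.997. The month terms that absorb forgetting also absorb most of this.

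**6. The 9.5 table.** A control woman's shortest possible recall is the time from her cohort's implementation date to 1 September 2022: about 8 months in cohort 1, 6 in cohort 2, 4 in cohort 3 and under 2 in cohort 4. After 11 July 2022 only cohort 5 supplies controls. Short-recall controls therefore come from later months and later cohorts, and long-recall controls include cohorts 1 and 2 (111 + 422 = 533 of 2,764, or 19%). A raw rate by recall month mixes forgetting with calendar trend and hospital mix.

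**The case against.** The SAP is open about this weakness. It admits differential recall (section 9), gives it a section of its own and lists it as a key limitation. Only 4.2 states the direction flatly, and no decision rule uses it. Two of the three call orders above leave the planned OR closer to the null than the truth. Forgotten events also cost power, so a true effect can be harder to detect whatever the bias. All of this stands. It supports a statement about power, or about the crude comparison, but not a known direction for the adjusted OR.

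A reader might infer that the conservative claim is false, or that the bias favours the intervention. The documents do not support that: the direction is unestablished, not refuted, and the call order that would settle it is not given.

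A reader might also infer that the open window reverses the bias in the primary estimate. Step 5 shows little such effect under common call timing. If late events were equally likely in both conditions they would dilute a real effect: adding an assumed 2 points to each rate turns 12% against 9% into 14% against 11%, an OR of (0.11/0.89)/(0.14/0.86) = 0.76. The wording about the period since discharge stands in the data dictionary, for the drainage item only. The form asks about drainage in the present tense and is headed for a call at 30 days. That auditors counted later events is possible, not documented.

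**Conclusion.** The concern holds in this form: the conservative direction is argued from a crude comparison and is not established for the month- and cohort-adjusted OR. If call timing was unrelated to cohort, little recall bias remains in either direction. If it was related, the sign follows the call order. At 6% loss per month and with cohorts called in sequence, the OR shifts by about 4 to 6% either way, against about 48% for the crude OR. These sizes rest on the assumed recall loss, post-discharge share, even accrual and call orders. The structural conclusion rests only on the model in SAP 7.1 and the missing call order.

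The 9.5 table cannot support the claim. The missing onset date and late-event rule bear mainly on crude rates, that table and the outcome definition. The one-year limit is contradicted by the SAP's own dates. The sponsor should make these changes; none of them invalidates the primary model.

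**What to change.** 1. Withdraw the directional claim in SAP 4.2, 9.5 and 10, or limit it expressly to the unadjusted comparison.
2. Report surgery-to-call time by arm within surgery month and cohort, and describe the order in which auditors called.
3. Replace the raw control-only table in 9.5 with a recall slope adjusted for hospital and surgery month. Calls spanned seven months, so women with the same surgery month can differ in recall. If they hardly do, say so.
4. Add one Aim 1 sensitivity model with days from surgery to the successful auditor call as a covariate.
5. State how events after day 30 were handled. If they cannot be separated, label the post-discharge component as SSI reported since discharge.
6. Correct the recall range to about 13 to 19 months for the earliest patients.

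I would not restrict Aim 1 to calls within six months. That removes every control in cohorts 1 and 2 and, with even accrual, at least about 1,922 of 2,764 controls (70%).

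The cost is SAP wording and a few model runs. Both dates are on the form and 9.5 already computes the interval. The recall-adjusted OR will lose some precision because recall time is correlated with surgery month. The slope may also partly reflect who was hard to reach.

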#### 4.3. Loss to follow-up among data collectors and auditors

Because the auditors were collecting data up to a year after the surgery, their follow-up rates are much lower than the data collectors. Table 3 shows the stepped wedge sample for patients with follow-up data from the auditors. Again, the balance in each cohort is still appropriate, and the overall balance across conditions is 49% control and 51% intervention.

Table 3: Achieved stepped wedge sample with auditor follow-up data, total and by cohort

| Hospitals        | Implemen-
tation date | N     | 2021           |   |   |   |   |               |          |          | 2022 |            |                     |          |   |          |   |   | 2023 |   |  |
|------------------|--------------------------|-------|----------------|---|---|---|---|---------------|----------|----------|------|------------|---------------------|----------|---|----------|---|---|------|---|--|
|                  |                          |       | A              | S | O | N | D | J             | F        | M        | A    | M          | J                   | J        | A | S        | O | N | D    | J |  |
| 1 Hospital 1     | 28-Dec-21                | 652   | 111, 17%       |   |   |   |   |               | 545, 83% |          |      |            |                     |          |   |          |   |   |      |   |  |
| 2 Hospital 2 & 3 | 1-Mar-22                 | 1,257 | 422, 33%       |   |   |   |   |               |          | 851, 67% |      |            |                     |          |   |          |   |   |      |   |  |
| 3 Hospital 4 & 5 | 9-May-22                 | 1,186 | 600, 50%       |   |   |   |   |               |          |          |      | 603, 50%   |                     |          |   |          |   |   |      |   |  |
| 4 Hospital 6 & 7 | 11-Jul-22                | 1,364 | 783, 56%       |   |   |   |   |               |          |          |      |            |                     | 607, 44% |   |          |   |   |      |   |  |
| 5 Hospital 8 & 9 | 13-Sep-22                | 1,066 | 848, 79%       |   |   |   |   |               |          |          |      |            |                     |          |   | 222, 21% |   |   |      |   |  |
| Total            |                          | 5,525 | 2,764, 49%     |   |   |   |   |               |          |          |      | 2,828, 51% |                     |          |   |          |   |   |      |   |  |
|                  |                          |       | Control period |   |   |   |   | Run-in period |          |          |      |            | Intervention period |          |   |          |   |   |      |   |  |

However, the overall N's for auditors in table 3 are smaller than those for data collectors. Table 4 shows the follow up rate for each group, by control or intervention condition. While the auditors yielded plausible SSI estimates, their follow-up rates were only 52% overall, which we attribute to the late date that they began and the challenging context that Ethiopia represents.

Table 4: 30-day follow-up rates by control and intervention condition, data collectors vs. auditors

| Cohort | Control condition      |                       |                |                       |                | Intervention condition |                       |                |                       |                |
|--------|------------------------|-----------------------|----------------|-----------------------|----------------|------------------------|-----------------------|----------------|-----------------------|----------------|
|        | N enrolled in facility | Data collectors       |                | Auditors              |                | N enrolled in facility | Data collectors       |                | Auditors              |                |
|        |                        | N with follow-up data | Follow-up rate | N with follow-up data | Follow-up rate |                        | N with follow-up data | Follow-up rate | N with follow-up data | Follow-up rate |
| 1      | 230                    | 223                   | 97%            | 111                   | 48%            | 772                    | 761                   | 99%            | 545                   | 71%            |
| 2      | 948                    | 904                   | 95%            | 422                   | 45%            | 1,704                  | 1,611                 | 95%            | 851                   | 50%            |
| 3      | 959                    | 911                   | 95%            | 600                   | 63%            | 975                    | 912                   | 94%            | 603                   | 62%            |
| 4      | 2,002                  | 1,981                 | 99%            | 783                   | 39%            | 1,087                  | 947                   | 87%            | 607                   | 56%            |
| 5      | 1,576                  | 1,542                 | 98%            | 848                   | 53%            | 413                    | 361                   | 87%            | 222                   | 54%            |
| Total  | 5,715                  | 5,561                 | 97%            | 2,764                 | 48%            | 4,951                  | 4,592                 | 93%            | 2,828                 | 57%            |

30-day follow-up was lower among the auditors compared to the data collectors, with only 48% of patients followed up in the control condition and 57% in the intervention condition. Because the phone calls happened toward the end of the study, the calls in the intervention condition were much closer temporally the enrolled patients' operations compared to the calls to patients enrolled in the control condition, which made it difficult for the auditors to reach control-period patients.

While we recognize measurement problems with both the data collectors' and auditors' data, after consideration we decided to use the auditors' data for all follow-up measures, which include the primary outcome. We will construct some sensitivity analyses to test this decision, as described below. As we have also lost power within the study due to this loss to follow-up, we will add a sensitivity analysis using multiple imputation for the dependent variable to help recapture some statistical power, as described below.

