## 4. Audit of 30-day follow-up data

### 4.1. Background

In May 2022 the study team became concerned that SSI rates at 30-day phone follow-up were too low relative to lived experiences of Ethiopian clinicians and published data on SSI rates in Ethiopia following caesarean section, calling into question the quality of the follow-up data. We were concerned the data collectors were missing a significant number of SSI on 30-day follow-up. Although we had robust in-hospital SSI data, most SSIs occur after hospital discharge, and total (inpatient and 30-day) SSI rate is the primary outcome of this study. For these reasons, we decided to audit outcomes on the entire sample using staff with more clinical and research training. Beginning in August 2022, we recruited and trained general practitioners on the 30-day follow-up data collection tool, and between September 2022 and March 2023, these auditors called all patients and re-collected 30-day follow-up data retrospectively. The original set of data collectors continued to collect follow-up data as well.

In this SAP, we refer to the initial group of workers whose data was called into question as the “data collectors,” and the more trained workers who replicated the follow-up calls as the “auditors.”

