### *CS population with follow-up*

All CS patients enrolled in the study who have complete 30-day follow-up data collected by the auditors.

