### 9.2 Sensitivity to fieldwork staff

In our original follow-up data collected by the data collectors, one hospital had an SSI rate around 9%, which is compatible with national reports of SSI data. Our first sensitivity analysis will be to run the main model predicting SSI but include the follow-up data according to the data collectors for this single hospital rather than the data collected by the auditors.

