### 9.4 Sensitivity to loss to follow-up

First, we will construct a demographic table comparing the women who were followed up by the auditors against those who were not. This may identify some imbalances that may introduce bias.

Next, we will use multiple imputation methods to model the primary outcome with the total CS population. We will generate an imputed value and 95% CI for the OR of SSI in the intervention versus control period.

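### The imputation meant to regain power names no auxiliary outcome data, has no rule for ward-recorded infections in unreached women, and the data-source check covers one selected hospital

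*Combined protocol and SAP*

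**What the plan says.** SAP 4.1 defines the primary outcome as total SSI, inpatient plus 30-day, and describes the ward data favourably: "Although we had robust in-hospital SSI data, most SSIs occur after hospital discharge". SAP 4.3 then takes all follow-up measures, including the primary outcome, from the auditors. Section 6 defines the population for Aim 1 as "All CS patients enrolled in the study who have complete 30-day follow-up data collected by the auditors".

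On the resulting loss, SAP 4.3 says of the auditors that "their follow-up rates were only 52% overall", "with only 48% of patients followed up in the control condition and 57% in the intervention condition". Its remedy is: "we will add a sensitivity analysis using multiple imputation for the dependent variable to help recapture some statistical power". The only other specification is in section 9.4 (Sensitivity to loss to follow-up): "we will use multiple imputation methods to model the primary outcome with the total CS population", to give an odds ratio with a 95% CI. The same section plans a demographic table of reached against unreached women, not split by condition.

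SAP 4.3 also promises sensitivity analyses that test the decision to use the auditors. Section 9.2 takes the one hospital where the collectors' SSI rate was about 9% and will "include the follow-up data according to the data collectors for this single hospital rather than the data collected by the auditors".

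**The concern.** Three things do not fit together.

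- **Purpose.** When only the outcome is missing, imputing it from covariates already in the analysis model returns the complete-case answer plus simulation noise. Power is regained only if the imputation uses other data that predict the missing outcome. The SAP names none.
- **Known events.** A woman with an SSI on the ward form has had the primary event whether or not an auditor later reached her. Section 6 leaves her out of Aim 1 if she was not reached, and nothing in 9.4 says that her event is carried into the imputation.
- **Choice of source.** A swap in one hospital, picked because its rate looked plausible, says nothing about the source decision in the other eight.

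At stake is whether these analyses can show anything about the nearly half of patients without auditor data.

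**Working it through.** **1. Reproduce the plan's follow-up rates (SAP Table 4; all enrolled patients, cesarean plus Ob/Gyn).**
- Auditors: (2,764 + 2,828) / 10,666 = 5,592 / 10,666 = 52.4%, matching the stated 52%. By condition: 2,764 / 5,715 = 48.4% and 2,828 / 4,951 = 57.1%, matching 48% and 57%.
- Collectors: (5,561 + 4,592) / 10,666 = 10,153 / 10,666 = 95.2%.
- The N column of Table 3 sums to 5,525, while its control and intervention cells sum to 5,592. Using 5,525 gives 51.8%, so the point is unaffected, but the tables should be reconciled.

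**2. Size of the gap.**
- Control: 5,715 − 2,764 = 2,951 (51.6%). Intervention: 4,951 − 2,828 = 2,123 (42.9%). Total: 5,074 (47.6%).
- Lower bound on patients with a collector record but no auditor record: collector count minus auditor count in each cell of Table 4. Control: 112 + 482 + 311 + 1,198 + 694 = 2,797. Intervention: 216 + 760 + 309 + 340 + 139 = 1,764. Total: 4,561, and 4,561 / 5,074 = 89.9%.

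**3. Information with and without auxiliaries.** Inputs: 12% control (protocol power calculation), 9% intervention (within the protocol's 8% to 9.5%), two-sided alpha 0.05 (sidedness assumed), clustering and period effects ignored.

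SE(log OR) = √[1/(n₀p₀(1−p₀)) + 1/(n₁p₁(1−p₁))]
- Complete cases: √[1/(2,764 × 0.12 × 0.88) + 1/(2,828 × 0.09 × 0.91)] = √(0.003426 + 0.004318) = 0.088.
- Full data: √[1/(5,715 × 0.12 × 0.88) + 1/(4,951 × 0.09 × 0.91)] = √(0.001657 + 0.002466) = 0.064.
- Imputation with analysis-model terms only: the missing-information fraction is 1 − 0.004123/0.007744 = 0.47. With 50 imputations the variance is the complete-case variance times about 1 + 0.47/50, so SE ≈ 0.088 × √1.0094 = 0.0884.

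A simulation (2,000 runs, 50 imputations, Rubin's rules, outcomes missing at random within condition) agrees. For the auxiliaries it assumes collector sensitivity 0 to 50%, specificity 99 to 100%, and ward capture of 0 to 30% of SSIs. None of these figures is in the documents.

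| Analysis | SE, 12% v 9% | Power, 12% v 9% | Power, 12% v 10% |
|---|---|---|---|
| Complete cases | 0.088 | about 95% | 67% |
| Imputation, analysis-model terms only | 0.088–0.089 | about 95% | 67% |
| Imputation with ward and/or collector data | 0.076–0.085 | 96–99% | 74% |
| Full data | 0.064 | 99.9% | 91% |

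The 74% uses collector sensitivity 25% and ward capture 20%. Because clustering is ignored, the absolute powers are optimistic; only the comparison between rows counts.

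**4. Which outcomes are settled without the auditors.** A positive ward record settles the outcome at 1. A negative one does not, since SAP 4.1 says that most SSIs occur after discharge. A collector's negative answer does not either: SAP 4.2 reports control rates of 3.0% or lower in 8 of 9 hospitals and judges these data not valid. For most unreached women the outcome is therefore truly missing, and the collector answer is an imperfect predictor of it.

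**The case against.** The strongest reply is that the SAP is silent here, not wrong. The imputation model is unspecified, so the analysts may intend to use the ward and collector data, and one that did would regain some power. That stands: it would be too strong to say that the imputation cannot help. But a plan that gives power as the reason for imputing should name what supplies it.

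A reader might infer that the ward record has been set aside, or that most imputed outcomes are already known. The documents support neither. The SAP calls the ward data robust and never says that ward-positive women are treated as missing; it gives no rule for those the auditors did not reach. Only ward-positive outcomes are settled.

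A reader might also infer a definite bias in the odds ratio from the unequal loss. The documents give no data on whether women with SSI were easier or harder to reach. The primary model has an 18-level month term, which absorbs selection on SSI that depends only on the month of surgery. Bias would need selection that differs by condition or cohort within a month. The loss is also uneven: auditor reach was 63% v 62% in cohort 3 and 53% v 54% in cohort 5, so the pooled gap comes from cohorts 1, 2 and 4.

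Other checks exist. Section 9.3 drops each hospital in turn, 9.5 examines recall time, and section 10 names loss to follow-up as a major limitation. These stand, but 9.3 keeps the auditor outcome, 9.5 studies reached women only, and section 10 compares demographic and clinical characteristics, not ward SSI.

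**Conclusion.** The point holds as a gap in two sensitivity analyses. As written, the stated purpose of the imputation is not met: without auxiliary outcome data the standard error stays at about 0.088 and power does not move. With the ward and collector items the gain is real but moderate, for example 67% to 74% at 12% v 10%, under the assumed accuracies. No rule preserves ward-recorded SSIs for unreached women, and section 9.2 leaves the source decision untested in eight of nine hospitals.

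The 47.6% missing and the 90% with a collector record cover all enrolled patients; the cesarean-only figures may differ. The number of ward-recorded SSIs among unreached women is not given, so how many events are affected is unknown. Severity is should-fix, since the Aim 1 estimate does not depend on the imputation.

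**What to change.** **Section 9.4**
- Set the outcome to 1 for any ward-recorded SSI. Impute the rest using the ward wound and antibiotic items, the collectors' day-30 answers, hospital, month of surgery, condition and the eight controls.
- Compare reached with unreached women within each condition, and include ward-recorded SSI in the table.
- State here and in 4.3 that any gain in power depends on these auxiliaries.
- Optionally, add a delta shift for outcomes not missing at random.

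**Section 9.2**
- Keep the one-hospital analysis, and also refit the primary model with the collectors' outcome in all nine hospitals. Report it as a sensitivity analysis, with its known under-reporting stated.

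**Cost.** SAP wording and a few more model runs on data already held. The drawback is reliance on a measure that under-reports. An auxiliary variable need not be unbiased to be useful, but the nine-hospital refit must be read with that in mind.
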